**Methods:**

A randomized controlled trial with blinded assessors and intention-to-treat analysis will be undertaken. We will recruit 82 older adults, 60 years or over who have suffered a hip fracture due to a fall in the previous 6 to 24 months. Participants randomized to the Intervention Group (IG) will undertake a physical exercise program involving progressive and challenging balance training and neuromuscular and functional training of the lower limbs, conducted at home by physiotherapists, once a week, lasting about one hour, in the first, second and third month after randomization and will be taught to perform exercises at home, twice a week, using a booklet. Visits to monitor and progress the home exercise program will be conducted once a month, from the fourth to the sixth month and each 2 months until the end of the follow up at the 12^th^ month, i.e., a total of 18 sessions. Participants will receive monthly phone calls to encourage exercise adherence. The control group will receive usual care. The primary outcome will be mobility-related disability and participants will be assessed at baseline, and at 3 months, 6 and 12 months. Participants will receive monthly phone calls to ask about falls and exercise adherence. Adverse effects will be monitored.

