In the first session the physiotherapist will choose two exercises that best address the participant’s functional goals and will add more exercises each week according to the participant’s ability, rate of improvement and motivation. The degree of balance challenge will be progressed in terms of reducing the base of support, the use of hands and the inclusion of multisegmental coordination exercises. Participants will be receive recommendations on how to perform the exercises safely, such as standing near of a table or in the corner of a room, so they can promptly use hands for protection if they start to fall. Those who are frailer will be encouraged to perform exercises under supervision of a caregiver. Participants will receive a detailed booklet, containing photos and instructions for the exercises.

Adverse effects related to the intervention that interfere in the activities of everyday life for more than 48h or require medical attention will be recorded and monitored (pain, discomfort, swelling, etc.). During home-visits the physiotherapist will check how the participant is performing the exercises and progress the exercises if necessary. Participants will receive monthly phone calls to encourage exercise adherence and to collect information about falls and their consequences. Participants will be asked reasons for non-adherence to exercises.

Participants will receive a diary logbook to record the number of falls a week and a guidance booklet containing information about prevention of falls (involving person, environmental and occupational factors), prevention of fractures and bone health. This group will also receive usual health care.

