#### Control group

This group will receive usual care; so will not be disadvantaged by participating in the study. Usual care will be what the participant receives as part of the network of health care which he/she is part of. The participants will receive a diary falls logbook and a guidance booklet containing information about prevention of falls, fractures and bone health. Control group participants will receive monthly phone calls requesting information about falls and their consequences.

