### Outcomes

All participants will be assessed in their homes at four different timepoints: at baseline and after 3, 6 and 12 months of randomization.

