*Physical activity level* will be measured by the self-reported Incidental and Planned Exercise Questionnaire - IPEQ_W [26], ten questions designed to measure physical activity planned and unplanned for older people. The version estimates the intensity of physical activity during the last week will be used. The participant will be questioned for the frequency (every day, 3–6 times per week, twice a week, once a week or less than once per week) and duration of activity (less than 15min per day, more than 15min and under 30min per day, more than 30min and less than 1h, less over 1h and 2h per day more and less than 4h per day 2h, 4h, and daily or more). The total score is derived by multiplying the frequency categories by categories of activity duration, expressed in hours per week.

*Occurrence of falls* will be assessed by monthly phone calls to participants who will be encouraged to use to diary to record the number of falls each day. A structured questionnaire will be used to identify possible falls and their consequences. The intervention group will be compared to control group at 6 and 12 months follow-up in relation to the number of falls (primary outcome) and the proportion of fallers.

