#### Sample characterization

*Functional Comorbidity Index* [27] is an 18-item scale designed to assess comorbidities related to physical function rather than mortality. Each scale item receives 1 point if the patient reports the disease.

*Cognitive function* will be assessed through the Montreal Cognitive Assessment Test (MoCA Test) [28], a battery of tests to detect mild cognitive impairment. The test takes 10min and the maximum score is 30 points. The test assesses different cognitive domains: attention and concentration, memory, language, visuoconstructional skills, conceptual thinking, calculations and orientation.

*Depressive symptoms* assessed by the Geriatric Depression Scale (GDS) [29], an instrument designed to detect depression in the older people. The short version contains 15 items and is the most used in clinical settings due to its rapid application. Each answer has a score of 0 or 1, and a final score above 6 points is considered to be indicative of depression.

*Fall-related self-efficacy*, assessed by the Falls Efficacy Scale International (FES-I) [30] a scale of self-efficacy of fall avoidance during activities of everyday life, which has 16 items with scores ranging from 1 to 4 (maximum total score 64) and a cutoff score of 31 points.

*Nutritional status*, assessed by the Mini Nutritional Assessment (MNA) [31] a questionnaire consisting of two parts: Screening and Overall Assessment. The screening consists of 6 basic questions about weight loss, BMI, mobility and neuropsychological problems. The score in the first part of the assessment can vary from 0 to 14 points. If the score is less than 12, the researcher must continue through the second part of the questionnaire, composed of more specific questions on nutrition and physical assessment. The sum of 18 questions can provide a maximum score of 30. The person with a score greater than or equal to 24 points is considered well-nourished, a score of 17–23.5 is considered at risk for malnutrition, and a score of less than 17 classifies the person as malnourished.

*Number of regular medications*, prescribed by a doctor, in the last 3 months will be computed, except vitamins and other medications for sporadic use (analgesics, for example). The use of psychotropic medications will be specifically recorded.

*Hospitalization and care in emergency department*: duration and reason for hospitalization and duration of stay in the emergency department during the study period.

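### Non-fall adverse effects such as pain and swelling are recorded, as written, only in the intervention arm and only if related to the intervention, so they cannot be compared between arms

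*Protocol article*

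**What the plan says.** The Intervention group section defines what counts as an adverse effect: "Adverse effects related to the intervention that interfere in the activities of everyday life for more than 48h or require medical attention". These events "will be recorded and monitored (pain, discomfort, swelling, etc", the bracket giving the kinds of complaint meant. The same section describes the calls to that arm: "Participants will receive monthly phone calls to encourage exercise adherence and to collect information about falls and their consequences".

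The Control group section describes usual care, a falls diary, a guidance booklet and calls: "Control group participants will receive monthly phone calls requesting information about falls and their consequences". It contains no rule for adverse effects.

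The Methods paragraph of the Abstract adds one general sentence, "Adverse effects will be monitored", which names neither an arm nor a method.

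Other data that bear on harm are not limited to one arm. Under Secondary outcomes, "The intervention group will be compared to control group at 6 and 12 months follow-up in relation to the number of falls", together with the proportion of fallers. Under Sample characterization the article lists "duration and reason for hospitalization and duration of stay in the emergency department during the study period". Under Outcomes, "All participants will be assessed in their homes at four different timepoints": baseline and 3, 6 and 12 months.

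**The concern.** The rule has two conditions, one on severity (more than 48 hours of interference, or medical attention) and one on cause (related to the intervention). The severity condition could be applied equally in both arms. The causal one cannot, because it excludes the control arm by definition. Within the intervention arm it calls for a judgement made with allocation known, since participants and therapists are unblinded, and without a control rate to judge against.

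Participants are 60 or older and in the late phase after a surgically treated hip fracture. Pain, swelling and medical visits are plausible in such people without any exercise. A one-arm, attribution-filtered count can therefore err in either direction: background complaints may be blamed on the programme, or real effects may be put down to the old fracture.

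What is at stake is the tolerability side of the conclusion. The programme combines progressive ankle-weight strengthening with challenging balance work, and the Discussion hopes that it may enter the public health system. Musculoskeletal complaints are an obvious safety question for such a programme. Analysis cannot repair the gap afterwards, because unfiltered events in the control arm would not have been asked for.

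**Working it through.** **1. The plan's own figure.** The article gives no adverse-effect rate. Its only sample-size figure is 41 per group, under Sample size calculation: difference 1.0, SD 1.48, 80% power, 5% significance (taken as two-sided), up to 15% loss.

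n = 2 × [1.48 × (1.960 + 0.842) / 1.0]² = 34.4, that is 35 evaluable per group. Allowing for loss, 34.4 / 0.85 = 40.5, so 41. The stated figure reproduces, and this point does not change it.

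**2. What each arm is asked, as written.**

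| Item | Intervention | Control |
|---|---|---|
| Pain, discomfort, swelling over 48 h or needing medical attention | Recorded if related to the intervention | No rule stated |
| Falls and their consequences, monthly calls | Yes | Yes |
| Hospitalization and emergency care | Not limited by arm | Not limited by arm |
| WHODAS 2.0 and WHOQOL-bref at 0, 3, 6 and 12 months | Yes | Yes |
| Therapist home visits | 18 | None |

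Only the first row lacks a control counterpart as a harm measure. The last row is a difference in opportunity: the intervention arm has 18 visits at which a complaint may come to notice. The calls do not add to this difference, because the article does not say that the calls to either arm ask about adverse effects.

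**3. Why a one-arm count does not give the excess risk.** Excess = p(intervention) − p(control), and p(control) is not observed. Suppose, for illustration only, that 30% of the intervention arm has a qualifying problem:

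| Assumed control rate | Excess risk (points) |
|---|---|
| 0% | 30 |
| 5% | 25 |
| 10% | 20 |
| 20% | 10 |
| 30% | 0 |

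The same intervention count is compatible with every row.

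**4. What asking both arms would give.** Half-width of the 95% confidence interval for the risk difference = 1.96 × √[2p(1 − p)/n], with p assumed to be 0.20 in both arms.

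- n = 41: 1.96 × √(0.32/41) = 0.173, about ±17 points.
- n = 35 (41 × 0.85 = 34.85): 1.96 × √(0.32/35) = 0.187, about ±19 points.

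In terms of power with 41 per arm (two-sided 5%): about 86% for 30% against 5%, 62% for 30% against 10%, and 18% for 30% against 20%. Only a large excess would be detected reliably.

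**The case against.** A reader might infer that no harm at all can be compared between arms, or that the trial can say nothing about problems caused by the programme. The article does not support that. Falls, a central harm for challenging balance work in this population, are collected monthly in both arms, together with their consequences, and their rate is compared by negative binomial regression. Hospitalization, with its reason, and emergency stay are recorded without restriction by arm, which covers the more serious part of needing medical attention. WHODAS 2.0 rates difficulty partly on discomfort or pain and is collected in everyone; with blinded assessors, it gives an indirect but randomized signal. All of this stands and limits the point to non-fall complaints. None of it supplies a control count of pain or swelling that meets the stated threshold.

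A reader might also set a large number of intervention contacts against none in controls, or expect background events alone to produce 4 to 12 intervention cases (41 × 0.10 = 4.1; 41 × 0.30 = 12.3) against zero. Neither comparison holds. Counting the intervention calls as adverse-effect contacts but not the control calls treats the same silence in the text differently by arm. The 4 to 12 is an upper bound: it rests on an assumed 10–30% background rate and on the attribution filter failing completely.

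It can also be said that this is a condensed article, that call scripts and adverse-event forms may sit in a fuller document, that the Abstract sentence names no arm, and that no between-arm comparison of adverse effects is promised. This has some weight: restriction to one arm is partly read from where the rule is placed. But placement is not the whole argument. The causal condition is stated outright, and usual-care participants cannot meet it wherever the sentence stands. The Abstract sentence does not change the definition.

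Finally, symmetric questions do not remove reporting bias, because participants know their group. That stands as a limit on what the fix achieves.

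**Conclusion.** The point holds for non-fall adverse effects such as pain, discomfort and swelling that limit daily activities for more than 48 hours or need medical attention. As written, they are recorded only for the intervention arm and only when related to the intervention. They have no like-for-like control count, and their excess risk cannot be estimated.

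It does not extend to falls, hospitalization or emergency care, and it leaves the primary SPPB analysis and the sample size untouched. Its size cannot be stated as a bias, because the article gives no event rate; the percentages used here are illustrative assumptions. What can be stated is the gain: from no estimate to one of about ±17 points (41 per arm) or ±19 points (35 evaluable) at an assumed 20% rate. The reading assumes that the article's rule is the one followed in the field. If a fuller protocol already asks both arms the same question regardless of cause, the article's text only needs correcting.

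This is a cheap improvement worth making, not a threat to the trial's main result.

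**What to change.** In the Intervention group and Control group sections, add the same structured question to the monthly calls already planned for both arms: any new or worse pain, discomfort, swelling or other problem since the last call that limited daily activities for more than 48 hours or needed medical attention.

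- Record every such event regardless of presumed cause. Enter attribution afterwards in a separate field.
- Compare arms on the proportion of participants with at least one call-reported event, as a risk difference with 95% confidence interval.
- List events noticed by therapists at home visits separately, so that the 18 extra visits do not inflate the intervention count.
- State in the report that participants were unblinded and that the estimate is imprecise.

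The cost is one question in calls that already take place and one additional table. The downsides are slightly longer calls, a higher raw number of reported events, and residual reporting bias. No treatment or clinical rule changes.

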#### Control group

This group will receive usual care; so will not be disadvantaged by participating in the study. Usual care will be what the participant receives as part of the network of health care which he/she is part of. The participants will receive a diary falls logbook and a guidance booklet containing information about prevention of falls, fractures and bone health. Control group participants will receive monthly phone calls requesting information about falls and their consequences.

### Outcomes

All participants will be assessed in their homes at four different timepoints: at baseline and after 3, 6 and 12 months of randomization.

#### Primary outcomes

Lower limb functionality will be measured by the Short Physical Performance Battery (SPPB) [20], that consists of three tests that assess static balance, walking speed and, indirectly, the strength of the lower limbs (sitting and standing from a chair unassisted). Each test has a score of zero (worst performance) to 4 points (best performance), totaling a maximum final score of 12 points. This instrument can predict negative consequences such as falls and the onset of disability in older people [21]. The use of walking aids will be allowed during the test if necessary.

#### Secondary outcomes

*Physiological risk of falls* will be measured by the Profile Physiological Assessment long version (PPA) [22, 23] which provides an overall score for risk of falling through a series of tests that evaluates the systems involved in the postural stability system. The results are computed using software specifically developed for the test that generates a report assessing the risk of falls. Physiological PPA tests include:○ Vision: low and high contrast, visual acuity and contrast sensitivity evaluated by the Melbourne Edge Test;○ The peripheral sensation tests: tactile sensitivity, measured by Semmes-Weinstein-type pressure esthesiometer;○ Proprioception: position sense of lower limbs;○ Muscle strength test: the muscle groups flexor and extensors of knee and ankle dorsi flexors will be assessed through a dynamometer;○ Reaction time test: Reaction time is measured in milliseconds using a modified computer, a mouse is used for response to finger pressure task and one pedal pressure for feet task;○ Balance test through a portable stabilogram, the swaymeter.

*Functional performance* measured by the self-reported WHO Disability Assessment Schedule (WHODAS 2.0) [24]. This scale measures health and functionality in 6 domains: cognition, mobility, self-care, interpersonal relationships, daily activities and participation. It was developed by WHO based on the International Classification of Functioning, Disability and Health (ICF), and it is not intended for any specific health condition. This short version assesses the difficulty degree of performing 12 activities in past 30 days, which can be classified as none, mild, moderate, severe and extreme (cannot be performed). The degree of difficulty reported is based on the presence of increased effort, discomfort or pain, slowness or the presence of some change in the way of doing the activity.

*Quality of life* measured by WHOQOL-bref [25], consists of 26 questions divided in 4 domains: physical, psychological, social relationships and environment. The questionnaire is based on the last 2 weeks of the participant and evaluated, for example, how safe he/she feel in her/his daily life and how satisfied is he/she with his/her ability to perform daily life activities.

*Physical activity level* will be measured by the self-reported Incidental and Planned Exercise Questionnaire - IPEQ_W [26], ten questions designed to measure physical activity planned and unplanned for older people. The version estimates the intensity of physical activity during the last week will be used. The participant will be questioned for the frequency (every day, 3–6 times per week, twice a week, once a week or less than once per week) and duration of activity (less than 15min per day, more than 15min and under 30min per day, more than 30min and less than 1h, less over 1h and 2h per day more and less than 4h per day 2h, 4h, and daily or more). The total score is derived by multiplying the frequency categories by categories of activity duration, expressed in hours per week.

*Occurrence of falls* will be assessed by monthly phone calls to participants who will be encouraged to use to diary to record the number of falls each day. A structured questionnaire will be used to identify possible falls and their consequences. The intervention group will be compared to control group at 6 and 12 months follow-up in relation to the number of falls (primary outcome) and the proportion of fallers.

#### Sample characterization

*Functional Comorbidity Index* [27] is an 18-item scale designed to assess comorbidities related to physical function rather than mortality. Each scale item receives 1 point if the patient reports the disease.

*Cognitive function* will be assessed through the Montreal Cognitive Assessment Test (MoCA Test) [28], a battery of tests to detect mild cognitive impairment. The test takes 10min and the maximum score is 30 points. The test assesses different cognitive domains: attention and concentration, memory, language, visuoconstructional skills, conceptual thinking, calculations and orientation.

*Depressive symptoms* assessed by the Geriatric Depression Scale (GDS) [29], an instrument designed to detect depression in the older people. The short version contains 15 items and is the most used in clinical settings due to its rapid application. Each answer has a score of 0 or 1, and a final score above 6 points is considered to be indicative of depression.

*Fall-related self-efficacy*, assessed by the Falls Efficacy Scale International (FES-I) [30] a scale of self-efficacy of fall avoidance during activities of everyday life, which has 16 items with scores ranging from 1 to 4 (maximum total score 64) and a cutoff score of 31 points.

*Nutritional status*, assessed by the Mini Nutritional Assessment (MNA) [31] a questionnaire consisting of two parts: Screening and Overall Assessment. The screening consists of 6 basic questions about weight loss, BMI, mobility and neuropsychological problems. The score in the first part of the assessment can vary from 0 to 14 points. If the score is less than 12, the researcher must continue through the second part of the questionnaire, composed of more specific questions on nutrition and physical assessment. The sum of 18 questions can provide a maximum score of 30. The person with a score greater than or equal to 24 points is considered well-nourished, a score of 17–23.5 is considered at risk for malnutrition, and a score of less than 17 classifies the person as malnourished.

*Number of regular medications*, prescribed by a doctor, in the last 3 months will be computed, except vitamins and other medications for sporadic use (analgesics, for example). The use of psychotropic medications will be specifically recorded.

*Hospitalization and care in emergency department*: duration and reason for hospitalization and duration of stay in the emergency department during the study period.

